## Abstract

**Background/Objectives**: The global burden of inflammatory bowel diseases (IBDs) continues to rise, with up to 50% of patients experiencing extraintestinal manifestations. Cardiovascular diseases (CVDs) are of particular concern, ranking as the second leading cause of mortality in this population. Despite a comparatively lower prevalence of traditional cardiovascular (CV) risk factors, the persistent inflammatory milieu and immune dysregulation inherent to IBD may contribute to heightened CVD risk. In this study, following a review of the current literature, an ongoing prospective trial designed to clarify CV risk profiles in IBD patients is detailed. **Methods**: A cohort of patients with IBD is being enrolled for comprehensive baseline evaluation of CV risk factors, lifestyle metrics, and disease characteristics. The incidence of major adverse cardiovascular events (MACEs) will be tracked and contrasted with a gender- and age-matched non-IBD cohort over a 2-year follow-up period. In cases of MACE occurrence, a multi-omics analysis—including genomic, proteomic, transcriptomic, and microbiome profiling—will be performed, along with a parallel evaluation in matched IBD controls without MACE. An artificial intelligence (AI) framework will support the analysis of this complex dataset. **Results**: To date, over 150 patients with IBD have been enrolled, and detailed phenotypic data and biological samples have been collected. **Conclusions**: We aim to introduce an IBD-specific correction factor for existing CV risk scores upon study completion. This is particularly relevant for individuals under 40 years of age, who are often inadequately assessed by current risk stratification models

## 1. Introduction

Crohn’s disease (CD) and ulcerative colitis (UC), the principal forms of inflammatory bowel disease (IBD), are showing a rising global prevalence, affecting an estimated 7 million individuals and placing a substantial strain on healthcare systems [1,2]. Many patients experience progressive intestinal damage, with complications such as hospitalization, surgery, malignancy, and elevated mortality risk [3,4]. Up to 50% of patients also develop extraintestinal manifestations, and there is an increased predisposition toward other immune-mediated disorders [5,6]. Among these comorbidities, cardiovascular disease (CVD) stands out in significance, especially as the aging IBD population sees a growing incidence of CVD-related mortality—now the second leading cause of death [7,8,9].

Despite advances in therapy, approximately one-third of patients with IBD exhibit primary non-response, and nearly half experience secondary loss of response [10]. While CVD remains the foremost cause of death globally [11], patients with IBD are more susceptible to premature atherosclerosis and myocardial infarction, particularly during active disease phases [12]. Alarmingly, conventional CV risk models often fail to capture this elevated risk, suggesting an underestimation in this specific population [13]. A comprehensive systematic review of more than 2 million patients with IBD identified smoking (24.2%) and alcohol use (4.6%) as the leading lifestyle risk factors. The common comorbidities included hypertension (30%), diabetes (14.4%), dyslipidemia (18.4%), pre-existing CVD (22%), and renal impairment (10%) [14].

### 1.1. IBD and CVD: A Shared Pathogenesis

IBD arises from a multifaceted interaction of genetic predisposition, immune dysregulation, environmental exposures, and dysbiosis of the gut microbiota—culminating in heightened cytokine activity [3,4]. This sustained inflammatory and immune-activated state may foster cardiovascular complications even in the absence of prominent conventional CV risk factors [7,8,12].

Emerging evidence points to shared pathophysiological mechanisms between IBD and CVD, including genetic overlap (e.g., *NOD2*, *CDKN2B*, *stromelysin*, and *ApoE* polymorphisms), shared environmental triggers like smoking, and convergent immune pathways [15]. Disruption of both intestinal epithelial and vascular endothelial barriers through cytokines like TNF-α may provide a mechanistic link between gut inflammation and vascular pathology [16]. In addition, gut microbiota alterations commonly seen in IBD have been implicated in the pathogenesis of cardiovascular conditions such as atherosclerosis [17].

Although the SCORE2 model developed by the European Society of Cardiology remains the prevailing tool for CV risk estimation, it has not been extensively validated in IBD populations and does not account for the heightened inflammatory burden, unlike the 1.5 correction factor applied in rheumatoid arthritis [18].

### 1.2. Risk of Major Adverse Cardiovascular Events in Inflammatory Bowel Disease

Multiple studies have demonstrated a significantly higher incidence of MACEs in IBD populations, with increases ranging from 25% to 300% compared with matched controls. A pivotal study by Bernstein et al. involving over 88,000 participants (8072 with IBD) reported an elevated incidence rate ratio (IRR) for ischemic heart disease (IHD) in patients with IBD (IRR: 1.26; 95% CI: 1.11–1.44) [19]. Similarly, a Danish cohort study analyzing 4.5 million individuals, including 28,833 with IBD, found a sharply elevated IHD risk in the first year after diagnosis (IRR: 2.13; 95% CI: 1.91–2.38), with a continued increased risk over time (IRR: 1.22; 95% CI: 1.14–1.30) [20]. A U.S. database study of over 29 million individuals showed a 25% higher likelihood of myocardial infarction among patients with IBD (OR: 1.25; 95% CI: 1.24–1.27) [21]. Standard CV risk algorithms may underestimate this burden, as chronic systemic inflammation is central to pathogenesis of CVD in IBD [22,23]. Elevated risks of stroke and cerebrovascular events have also been documented [24,25], with C-reactive protein (CRP) serving as a potential inflammatory marker [25]. A meta-analysis encompassing cohort and case–control studies confirmed a 21% increase in stroke risk in patients with IBD (OR/RR: 1.21; 95% CI: 1.08–1.34) [26]. Young IBD patients are particularly vulnerable to ischemic strokes, especially during active disease phases [24,25,26]. Additionally, an increased incidence of atrial fibrillation may further amplify the cerebrovascular risk [27].

### 1.3. Impact of IBD Treatments on Cardiovascular Risk

Certain IBD treatments, particularly corticosteroids, may worsen cardiovascular profiles by inducing hypertension, insulin resistance, and dyslipidemia [28]. However, steroid use often reflects severe disease activity, a known risk factor for CVD itself. Conversely, Rungoe et al. reported that patients with IBD treated with 5-ASA exhibited a reduced risk of IHD (IRR: 1.16 vs. 1.36 for non-users; *p* = 0.02), with prolonged use linked to even lower risks (IRR: 1.08) [20].

TNF-α inhibitors may provide cardiovascular protection [29]. A large observational study found a lower incidence of acute arterial events (AAEs) among TNF inhibitor users (HR: 0.79), with a similar risk reduction for recurrent events (HR: 0.75) [30]. Thiopurines have shown similar protective effects.

Data on the cardiovascular safety of newer biological therapies available, such as vedolizumab, ustekinumab, mirikizumab, and risankizumab, remain limited; however, no concerning safety signals related to AAEs have been identified thus far.

Janus kinase (JAK) inhibitors, including tofacitinib, filgotinib, and upadacitinib, are among the most recent agents approved for moderate to severe ulcerative colitis and, in the case of upadacitinib, also Crohn’s disease. Clinical trials have noted reversible elevations in serum lipids, including total cholesterol, LDL, and HDL, during early treatment with tofacitinib [31]. Hypercholesterolemia is a known contributor to cardiovascular events, and concerns have been raised regarding MACEs associated with this drug class. The ORAL Surveillance trial, which enrolled rheumatoid arthritis (RA) patients aged ≥50 with pre-existing cardiovascular risk factors, found a higher incidence of MACEs in those treated with tofacitinib (5 or 10 mg twice daily) compared with those on TNF inhibitors (HR: 1.33; 95% CI: 0.91–1.94) [32].

Based on recommendations from the Pharmacovigilance Risk Assessment Committee (PRAC), the European Medicines Agency’s Committee for Medicinal Products for Human Use (CHMP), has advised limiting the use of JAK inhibitors in patients with elevated cardiovascular risk, reserving them for cases with no appropriate alternatives. Nonetheless, a meta-analysis reviewing the safety of JAK inhibitors across IBD and other immune-mediated inflammatory diseases (IMIDs) reported 30 studies assessing MACEs in 32,765 treated individuals (17 on tofacitinib, 6 on upadacitinib, 4 on baricitinib, and 3 on filgotinib), with a pooled incidence rate of 0.67 per 100 patient-years. The relative risk of MACEs was estimated at 1.07 (95% CI: 0.56–2.03) in the analysis of 22 controlled trials [33].

The following tables illustrate

–Established cardiovascular risk factors (Table 1);–Shared biological mechanisms that may drive IBD and cardiovascular disease (Table 1);–Treatment-related cardiovascular risks (Table 2);–Summary of key studies conducted on this topic (Appendix A) [34,35,36,37,38,39,40,41,42,43,44,45,46,47,48,49,50,51,52,53,54,55,56,57,58,59,60,61,62,63,64,65,66,67,68,69,70,71].

**Table 1 jpm-15-00418-t001:** Risk factors for IBD and cardiovascular diseases.

Traditional CV Risk Factors	Risk Factors for IBD	Shared Risk Factors for IBD and CVDs	Specific Risk Factors in IBD for CVDs
Obesity	Genetic factors	Dysbiosis	Inflammatory cytokines
Hypertension	Dysbiosis	Genetic factors	Oxidative stress
Age	Smoke (CD)	Smoke (CD)	Hypercoagulability
Smoke	Diet	? Diet	Endothelial dysfunction
Diabetes	? No breast feeding	? Stress	
Dyslipidemia	? Antibiotics abuse		
Family history of IHD or stroke	Family history of IBD		
? Stress			
? Diet			

IHD = ischemic heart disease; CD = Crohn’s disease. ? = conflicting data

**Table 2 jpm-15-00418-t002:** Impact of IBD therapies on main cardiovascular risk.

IBD Medications	Potential CV Effect
5-Aminosalicylic acid	↓ Inflammation, ↓ platelet activation ↓ CV complications
Corticosteroids	↑ CV Risk (? proxy of more severe IBD)
Thiopurines	↓ Inflammation, ↓ atherosclerosis and arterial events
Anti-TNFα	↓ Inflammation, ↓ atherosclerosis and arterial events
Vedolizumab	↓ Inflammation, limited data, no increased CV risk
Ustekinumab	↓ Inflammation, limited data, no increased CV risk
IL-23 inhibitors	↓ Inflammation, limited data, no increased CV risk
Anti-JAK	↓ Inflammation, ↑ CV risk in RA
SP1 Modulators	↓ Inflammation, limited data, no increased CV risk

RA = rheumatoid arthritis. ? = conflicting data. ↑ = increased. ↓ = reduced.

### 1.4. IBD and MACEs: Risk Prediction

There remains a critical need for robust assessment of MACE incidence in IBD, therapy-related risks and benefits, lifestyle influences, and disease activity (Appendix A) [34,35,36,37,38,39,40,41,42,43,44,45,46,47,48,49,50,51,52,53,54,55,56,57,58,59,60,61,62,63,64,65,66,67,68,69,70,71]. We have launched a prospective study involving a well-characterized IBD cohort, matched with controls by age and gender. Multi-omics profiling and AI-based analyses will be applied to refine traditional CV risk stratification and uncover novel biomarkers.

### 1.5. Dissecting the Complexity of CV Risk in IBD Patients

As summarized in the previous sections, there is still an unmet need to evaluate the real amount of CV risk in patients with IBD because of the lack of prospective trials, and the limitation of the available CV risk scores designed for an older background population compared to the patients with IBD. In addition, there is a lack of a systematic evaluation of other possible shared risk factors, such as genetic polymorphisms or dysbiosis, and more importantly, the need to evaluate the full systematic dataset with a hypothesis-free powerful methodology, such as AI-driven algorithms. For these reasons, an ongoing study designed to overcome these limitations is described here.

## 2. Materials and Methods

### 2.1. Study Population

Our first aim was to prospectively enroll a large cohort of IBD patients in the Unit of Gastroenterology of the Research Hospital San Donato Policlinic, San Donato Milanese (Mi), for 1 year to be compared with an age/gender-matched cohort under follow-up at the Unit of Cardiology of the same Institution. To this end, a set of specialized, privacy-preserving large language models (LLMs), coordinated by an agentic framework provided by Agora Labs [72], will be applied to different types of data sources containing records of patients under follow-up at the San Donato Policlinic to maximize enrollment. Specifically, the LLMs will extract clinical findings, diagnoses, disease activity indicators, family and social history items, past and current treatments, and other clinical data from all kinds of free-text notes. Under the clinicians’ supervision, such extracted data will drastically expand the underlying data pool and cohort size available for analysis. Data from both unstructured and structured sources will be harmonized to allow for multi-omics queries and model development, starting from descriptive statistics to the development of predictive algorithms. Following the signature of informed consent, all patients with confirmed IBD according with standard of care [3,4] will have a baseline evaluation of family and personal CVD risk factors with a standard questionnaire, including occurrence in family members of MACEs defined as ischemic heart disease (IHD), myocardial infarction (MI), stroke (ST), atrial fibrillation (AF), heart failure (HF), and thromboembolic events (TE). All patients will be evaluated with SCORE2 and the glyco-metabolic inflammatory axes. In case of the occurrence of a high CV risk score (>10 <20%), the carotid intima-media thickness (IMT) will be measured by Doppler ultrasound as a surrogate marker for subclinical atherosclerosis. In case of very high CV risk (more than 10% or more than 7.5% in subjects older than 69 years or younger than 50 years, respectively), the patient will be referred to the cardiologist (if not previously referred) for further investigations. To all patients, lifestyle modification measures will be given in written (i.e., stop smoking, minimize alcohol use, and follow a Mediterranean diet). Patients with IBD will undergo a careful baseline evaluation of disease activity and ongoing therapy, standard laboratory investigations, ileocolonoscopy, and biopsies as standard of care [3,4]. In addition, in all IBD patients, different biological materials (whole blood, plasma/serum, tissues, and stool samples) will be collected and stored in the Policlinic Biobank. All patients will then be followed for at least 2 years, and every year, a re-evaluation of IBD activity, ongoing therapy, lab tests, and monitoring of the occurrence of MACEs will be recorded. The enrollment of the study population will be performed according to the protocol approved by the local ethics committee (Milan 29/1/2025 CET 510-2024), which was recently also registered as NCT07095634.

The control cohort will be that of the CV-PREVITAL trial (a multicenter, prospective, randomized, controlled, open-label interventional trial—NCT05339841) designed to compare the effectiveness of an educational and motivational mobile health (mHealth) intervention versus usual care in reducing CV risk. The Cardiology Unit of IRCC Policlinico San Donato has already enrolled 1109 healthy individuals in this trial. These participants, who were free from known CVDs at baseline, have already completed a 1-year follow-up and are still under cardiological evaluation to monitor their CV health over time. The control group for the IBD cohort, matched for age and sex, will be extrapolated from this population.

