### 2.3. Prospective Evaluation

At the end of the 2-year follow-up, all patients in the IBD cohorts and the control population will be re-evaluated in terms of CVD risk using SCORE 2, the standard laboratory and cardiologic investigations will be repeated, and the occurrence of new MACEs will be reported. All patients with IBD will be regularly evaluated during the follow-up at 3–6 month intervals, and all will receive a clinical, endoscopic, and histologic evaluation at the end of follow-up. The subgroup of patients with the occurrence of MACEs and those with clinical and endoscopic remission will also repeat the transcriptomics and metagenomics evaluation.

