### 2.4. Objectives of the Study

The primary objective of the study will be to evaluate the basal CVD risk in our IBD population compared with the age- and gender-matched cohort of non-IBD patients.

The secondary objectives will be as follows:–Correlation of the basal CVD risk with multi-omics biomarkers, disease activity, lifestyle (i.e., diet, smoking) and therapy;–To evaluate the occurrence of MACEs at the end of follow-up in the patients with IBD and control populations;–To investigate the possible correlation between high CVD risk and MACE occurrence with multi-omics findings;–To identify possible biomarkers of increased CVD risk compared with the control population;–To establish possible correction factors to apply to the standard traditional CVD risk score to incorporate the IBD inflammatory burden.

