## 3. Results

No solid results of the ongoing study are given; only the status of recruitment at the time of writing is reported. In total, 167 patients with IBD have been enrolled with detailed phenotyping and bio-sampling.

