## 5. Conclusions

The exact underlying mechanisms of cardiovascular events in IBD remain poorly understood. More research is required to elucidate the complex interplay between inflammation, immune dysregulation, and CVD pathogenesis in IBD, which encompasses a spectrum of diseases with varying clinical phenotypes and courses. More studies are needed to understand these nuances and to guide targeted interventions. Existing studies primarily rely on observational or retrospective data, making it difficult to establish definite causal relationships between specific factors and CVD development. In this study, all consecutive patients with IBD will be evaluated for their basal SCORE 2 and complete disease characteristics and will undergo screening cardiologic investigations to assess potential cardiovascular issues. Following at least 2 years of follow-up, the whole cardiologic and gastroenterological assessment will be repeated, and the occurrence of MACEs will be investigated and correlated with the multi-omics assessment and control cohort. This in-depth evaluation will potentially reveal unexpected and silent underlying high risks for MACEs and direct the subjects, under the control of a cardiologist, to make significant changes in their lifestyle, diet, and therapy. More importantly, the multi-omics evaluation may reveal biomarkers of increased CV risk and suggest corrective factors for the standard CV risk score in this patient population.

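### The SCORE2 action cut-offs conflict: 'very high' starts below or level with 'high', and as printed a score of 20% or more at ages 50–69 triggers neither carotid IMT nor referral

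*Protocol article*

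**What the plan says.** Section 2.1 (Study Population) has every patient scored with SCORE2 and then gives two score-triggered actions in consecutive sentences.

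- **High risk:** "In case of the occurrence of a high CV risk score (>10 <20%), the carotid intima-media thickness (IMT) will be measured by Doppler ultrasound". No age condition is attached.
- **Very high risk:** the category is printed as "very high CV risk (more than 10% or more than 7.5% in subjects older than 69 years or younger than 50 years, respectively"), and the action is that "the patient will be referred to the cardiologist (if not previously referred) for further investigations".

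Other text bears on the same patients:

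- Section 2.1 adds: "To all patients, lifestyle modification measures will be given in written".
- Section 5 (Conclusions) says that all consecutive IBD patients "will undergo screening cardiologic investigations to assess potential cardiovascular issues".
- Section 2.3 says that at the end of follow-up "the standard laboratory and cardiologic investigations will be repeated".
- Section 2.4 lists a secondary objective that uses a high-risk label: "To investigate the possible correlation between high CVD risk and MACE occurrence with multi-omics findings".

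**The concern.** A two-step risk rule should have ordered categories, and its actions should not weaken as the score rises. The printed figures fail on both counts. Very high begins below high in the youngest patients and at the same point as high in the oldest. In the middle age band very high has no cut-off at all, while the 20% ceiling on high switches the IMT off.

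Two things are at stake. The first is participant work-up: at ages 50–69 the score-triggered rule does less for the highest scores than for middling ones. The second is labelling. Section 2.1 is the only place in the article that prints cut-offs for high risk. If the secondary objective in Section 2.4 takes its label from there, patients aged 50–69 with the highest scores would be grouped with those not at high risk.

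**Working it through.** The article gives no figure to reproduce here, so the check is to apply the two sentences as printed.

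**Inputs (all Section 2.1)**

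- IMT if 10% < score < 20%, at any age.
- Referral if age < 50 and score > 7.5%, or if age > 69 and score > 10%. The word *respectively* fixes this pairing.
- Ages 50 to 69 inclusive meet neither age condition.

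**Actions by age and score**

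| Age | ≤7.5% | >7.5 to 10% | >10 to <20% | ≥20% |
|---|---|---|---|---|
| Under 50 | none | referral | IMT + referral | referral |
| 50–69 | none | none | IMT | **none** |
| Over 69 | none | none | IMT + referral | referral |

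**What follows**

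1. *Order of categories.* Under 50, the very high floor (7.5%) lies below the high floor (10%), so a score of 8% is very high without being high. Over 69 both floors are 10%, so every high score is also very high.
2. *Step from >10 to <20% up to ≥20%.* At ages 50–69 action drops from IMT to none (1 of 3 age bands). In the other 2 of 3 it drops from IMT plus referral to referral alone.
3. *Referral at ages 50–69.* It occurs in 0 of 4 score bands.
4. *Labels.* High alone covers 3 of 12 cells and none of the 3 at 20% or more. High or very high covers 3 + 1 + 2 = 6 of 12 cells and 2 of the 3 at 20% or more; the one missing is ages 50–69.

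**Sensitivity to the reading**

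- *Ignoring the word respectively* (referral above 10% at any age, and above 7.5% if under 50 or over 69): the referral gap at ages 50–69 closes. Very high then starts at or below the high floor in all three age bands, and IMT still stops at 20%.
- *Taking 20% or more at ages 50–69 as very high:* the gap closes there too. The misordering under 50, the shared floor over 69 and the IMT ceiling all remain.

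**Relevance of the middle age band.** Table 3 gives the control pool's age as 55.9 ± 6.5 years (N = 1109). If those ages are roughly normal (an assumption), the limits for ages 50 to under 70 are z = (50 − 55.9)/6.5 = −0.91 and z = (70 − 55.9)/6.5 = 2.17. About 80% of the pool then lies in that band. Controls are to be matched to IBD patients on age, but this describes the control pool only and says nothing about how many IBD patients score 20% or more.

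**The case against.** The strongest reply is that the literal reading is not the natural one. A ceiling of 20% on high suggests that the next category begins there, and the two age-specific figures can be read as lower thresholds added for the youngest and oldest. A clinician would probably refer a 60-year-old scoring 25%. That is fair, but the article nowhere prints it, and the reading repairs neither the misordered floors nor the IMT ceiling.

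A second reply is that an article condenses the protocol approved by the ethics committee, which may hold a full table. This could excuse the absent cut-off for ages 50–69. It does not excuse printed figures that conflict with each other.

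Third, the practical harm is limited. Outside ages 50–69, no patient flagged by the score is left without action. Written lifestyle advice goes to everyone, IBD patients have cardiological screening, and investigations are repeated at the end of follow-up. These points stand and hold the severity down. The screening sentence gives no criterion for IMT or referral, however, and the repeat comes two years later.

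Fourth, Section 2.4 does not say that its high-risk label comes from Section 2.1, and such a definition is often left to the analysis plan. That is correct, so the labelling point is conditional and supports only a request for clarification.

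Finally, a count of cells is not a count of patients. The score bands follow from the printed cut-offs, but the cells are not equally populated, and the cell of ages 50–69 at 20% or more may be small.

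**Conclusion.** The cut-offs are wrong as written. The misordering of the two categories and the loss of IMT at 20% hold under every reading tried. The complete loss of score-triggered action at ages 50–69 with 20% or more holds on the literal reading, which is the only one consistent with the wording of the sentence.

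The size is 1 of 12 age-by-score cells with all action lost and 2 more with IMT lost but referral kept. The number of patients cannot be estimated from the article, because neither the ages nor the SCORE2 values of the IBD cohort are shown.

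The effect is on participant work-up and, conditionally, on a risk label in one secondary objective. The primary SCORE2 comparison and the power calculation do not use these cut-offs. The point is minor.

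**What to change.** Replace the two sentences with one age-by-score table (under 50, 50–69, over 69), confirmed by the study cardiologists:

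- In each band, very high lies above high. If 7.5% (under 50) and 10% (over 69) stay as referral floors, high must start lower in those bands.
- Ages 50–69 get an explicit referral cut-off that at minimum covers scores of 20% or more.
- Reaching 20% no longer removes an action in any band.
- The same categories are stated to define high CVD risk in the secondary objective.

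Then apply the table to patients already in the study. Section 3 reports that "167 patients with IBD have been enrolled with detailed phenotyping and bio-sampling"; these can be re-classified from recorded scores with no new measurement. Any who meet the corrected cut-off are referred, and any late IMT is flagged as non-baseline. Against the planned 300 IBD patients, 300 − 167 = 133 remained to be enrolled at the time of writing and would be classified correctly from the start. If enrolment has since closed (planned by the end of 2025), they are re-classified in the same way.

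The cost is low: a clarification of two sentences, probably a few more referrals or scans, and some IMT values that cannot serve as baseline.

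### Controls had to be free of known CVD at baseline and no such criterion is shown for IBD patients, so the unadjusted MACE comparison leans toward an IBD excess

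*Protocol article*

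**What the plan says.** Section 2.1 draws the controls from the CV-PREVITAL trial, for which the cardiology unit "has already enrolled 1109 healthy individuals in this trial". It adds: "These participants, who were free from known CVDs at baseline, have already completed a 1-year follow-up". On matching it says: "The control group for the IBD cohort, matched for age and sex, will be extrapolated from this population". Sections 3.2 and 4 bring in a propensity score, but again to obtain a control group matched on age and gender.

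For the IBD arm, section 2.1 says "all patients with confirmed IBD according with standard of care [3,4] will have a baseline evaluation", and the Conclusions say "all consecutive patients with IBD will be evaluated for their basal SCORE 2". Neither place, nor any other in the article, sets a CVD-free condition for these patients.

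Section 2.4 makes basal CVD risk, IBD versus matched controls, the primary objective. MACE occurrence in both populations and a correction factor for the risk score are secondary. Section 2.5 plans Kaplan–Meier curves, log-rank tests and two-group tests. It also plans a Cox model adjusted for confounders that it does not name. Its sample-size paragraph counts retrospective follow-up (2 years in one sentence, 3 in another) as well as 2 prospective years.

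**The concern.** Someone with known CVD cannot be a control but, as far as the article shows, can be an IBD patient. Prior CVD is expected to raise the rate of a further MACE, so the two arms can differ in MACE rate with no contribution from IBD. Balancing age and sex does not help, because the condition is absent from one arm by selection.

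The study exists to measure the IBD excess and turn it into a multiplier for cardiovascular risk scores. A selection artefact in the ratio would pass straight into that multiplier. Many of the effects cited in section 1.2 and Appendix A lie around 1.2 to 1.4, so even a moderate artefact could imitate them.

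**Working it through.** **Inputs from the article.** 300 IBD patients and 300 controls; control MACE rate 1% or 5% per year; target HR 2.5 or 1.6; significance level 5% (taken as two-sided); power by Cohen's h (all section 2.5). Pre-existing CVD in IBD: 22%, from a literature review cited in the Introduction. **Assumptions.** Share p of IBD patients with prior CVD: 5%, 10% or 22%. MACE rate ratio k for prior CVD against none: 2, 3 or 5; the article gives no value.

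**Step 1: reproduce the plan's power.** Cumulative risk is 1−exp(−rate×T). With h = 2·asin(√p₂) − 2·asin(√p₁), power = Φ(|h|·√(n₁n₂/(n₁+n₂)) − 1.96).

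- 1% per year, HR 2.5, T=4: risks 0.0392 and 0.0952, h≈0.2285, 0.2285×√150 = 2.80, power 79.9%.
- 5% per year, HR 1.6, T=4: power 77.6%.

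The stated 80% is therefore recovered (approximately, in the second case), but only with a 4-year window that includes 2 retrospective years.

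**Step 2: expected ratio with no IBD effect.** Controls have rate r. A share p of IBD patients has rate kr and the rest r, so the rate ratio is (1−p)+pk.

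| p | k=2 | k=3 | k=5 |
|---|---|---|---|
| 5% | 1.05 | 1.10 | 1.20 |
| 10% | 1.10 | 1.20 | 1.40 |
| 22% | 1.22 | 1.44 | 1.88 |

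At p=22% the imbalance is 0.22×300 = 66 IBD patients against 0 controls. Over 2 years at 1% per year, earlier depletion of the high-risk patients lowers the ratios slightly (1.88 becomes 1.85). To produce an apparent 1.6 at p=22%, k would have to be (1.6−0.78)/0.22 = 3.7; to produce 2.5, (2.5−0.78)/0.22 = 7.8.

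**Step 3: chance of a significant false excess.** The nominal chance in that direction is 2.5%. With 300 per group, k from 2 to 5, and the 2 prospective years at 1% per year, it is 3–5% for p=5%, 4–9% for p=10% and 5–24% for p=22%. For p=22% at 5% per year it is 12–68% over 2 years and 17–83% over 4 years.

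**Step 4: the retrospective window.** If those years fall before the controls' CVD-free baseline, controls can have no known event in them by selection, while IBD patients can. At 1% per year with equal true rates and no prior-CVD multiplier, 4 years of IBD counting against 2 control years gives 0.0392/0.0198 = 1.98; 5 years against 2 gives 0.0488/0.0198 = 2.46. If controls are at risk for 3 of those years, the ratios are 1.33 and 1.65. The article does not give the calendar dates needed to choose between these cases.

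**Step 5: power after restriction, 2 prospective years only.**

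| IBD vs controls | HR 2.5, 1%/yr | HR 1.6, 5%/yr |
|---|---|---|
| 300 vs 300 | 51.4% | 51.0% |
| 234 vs 300 | 46.4% | 46.0% |
| 234 vs 234 | 42.2% | 41.8% |

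Here 234 = 300×0.78. The first row shows that most of the fall from 80% comes from dropping the retrospective years.

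**The case against.** The article contains no eligibility list for the IBD arm. Enrolment follows a separate ethics-approved protocol that is not shown and may exclude prior CVD. That entry is open regardless of prior CVD is thus an inference. It is a reasonable one: counting retrospective MACE years makes sense only if IBD patients with earlier events may enter. It is still not a stated rule.

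Section 2.5 also plans balance checks by standardized mean differences, a Cox model adjusted for confounders and a possible propensity-matching sensitivity analysis. The confounder list may properly sit in the analysis plan, and a Cox model including prior CVD would largely remove the bias for prospective MACE. This limits the point to the unadjusted results, but does not dispose of it. The Kaplan–Meier, log-rank and two-group comparisons stay unadjusted. Matching on prior CVD cannot work either, because no control has it.

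The 22% comes from a literature review, not this cohort, and the article itself describes IBD patients as younger than the usual risk-score population. At p=5% and k=3 the artefact is only 1.10.

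A reader might go further and infer that the study will report an IBD effect even if none exists, or that the artefact alone reaches the target HR of 2.5. The documents support neither. The bias is in the expected estimate, significance is far from certain, and at p=22% the prior-CVD imbalance alone would need k near 8. A reader might also apply these ratios to the primary comparison. All the arithmetic concerns MACE; the article offers no basis for sizing a shift in SCORE2.

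**Conclusion.** The concern holds for the unadjusted between-cohort MACE comparison and for a correction factor derived from it. On the text shown, the arms are selected differently on prior CVD, age and sex matching leaves that in place, and the bias runs toward an IBD excess. Under no true effect the expected rate ratio lies between 1.05 and 1.88 for p of 5–22% and k of 2–5. That range rests on a borrowed prevalence and an assumed k, and on the IBD arm having no CVD exclusion in the full protocol. Counting retrospective years before the controls' baseline would add to it. The primary baseline-risk comparison uses the same unequal groups, but its bias cannot be quantified from the article.

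**What to change.** In sections 2.1 and 2.5, for every IBD-versus-control analysis (basal SCORE2, MACE, correction factor):

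- Apply the CV-PREVITAL criterion of no known CVD to IBD patients, using that trial's own definition, and match controls only to the patients who meet it.
- Set the same time zero in both arms, namely the CVD-free baseline date, and count MACE only after it. Leave retrospective years before that date out of the between-cohort comparison. Restriction alone is not enough: requiring no CVD at enrolment would make retrospective IBD events zero by construction and reverse the bias in that window.
- Keep IBD patients with prior CVD for the within-IBD omics analyses.
- Confirm that personal CVD history is captured. Section 2.1 says the questionnaire covers family and personal risk factors, but names MACE only for family members; the diagnoses extracted from clinical notes may fill the gap.

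This is a change to the analysis rules and does not require excluding anyone from enrolment. The cost is up to about 66 of 300 IBD patients in the comparison if 22% have prior CVD; keeping 300 CVD-free patients would need about 300/0.78 = 385 enrolled (334 at 10%, 316 at 5%). The power statement must be rewritten for the 2 prospective years: about 51% with 300 per group, about 46% with 234 against 300, and about 42% with 234 per group.
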